### Statistical analysis

Statistical methods are used to assess the quality of data, homogeneity of treatment groups, endpoints and safety of the two intervention groups. The confirmatory analysis is performed on the basis of an intention-to-treat (ITT) population and with respect to ITT principles.

Categorical data are summarized by means of absolute and relative frequencies (count and percent). Continuous data are presented by means of the following summary statistics: the number of observations, median, minimum, median and maximum. Wherever appropriate, data are visualized by box-whisker plots or histograms. The primary efficacy endpoint is amount of total intraoperative blood loss. The underlying two-sided null-hypothesis is that both study interventions lead to similar intraoperative blood loss:

$${\text{H}}_{0}:\mu 1-\mu 2=0$$

The alternative is that one intervention performs better than the other:

$${\text{H}}_{1}:\mu 1-\mu 2\neq 0$$

A confirmatory intention-to-treat analysis (2-sided test), including all patients as randomized, is performed on the amount of intraoperative blood loss between the two groups. Analysis of covariance (ANCOVA) is used to detect possible treatment differences with intraoperative blood loss as dependent variable, area of resection and CVP during transection as continuous covariates and type of intervention as factor. The sample size calculation is based on a two-sided t-test, and it can be assumed that evaluation with analysis of covariance has the same or even higher power.

Secondary endpoints will be analyzed in an exploratory way, using appropriate statistical methods based on the underlying distribution of the data. All analysis will employ SASα Version 9.1.

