### Study objectives and endpoints

The primary objective of this trial is to show that intraoperative blood loss during elective hepatic resection can be reduced by stapler hepatectomy as compared to the clamp-crushing technique.

The primary efficacy endpoint of the CRUNSH Trial is total intraoperative blood loss [ml], which is defined as blood loss from skin incision until closure of the skin. Intraoperative blood loss is measured according to the blood collected in the suction containers. Spilling water and ascites is subtracted. Furthermore, swabs are squeezed and their content will also be sucked and added to the fluid collected in the suction containers. To obtain a more precise estimate for the individual patient patient's individual transection area will be considered as a continuous covariate multivariate analysis. The transection area will be assessed using an imprint of the resected specimen on a paper sheet with a known density of 80 mg/m^2^.

To further evaluate efficacy and safety of stapler hepatectomy compared to the clamp-crushing technique, a set of general as well as surgical variables are documented as secondary endpoints [21]. The secondary endpoints of the trial are summarized together with their definition in Table 1.

**Table 1 T1:** Secondary endpoints of the CRUNSH Trial

Secondary endpoint	Definition and assessment of outcomes
*Blood loss during liver transection [mL]*	Blood loss from beginning of parenchymal transection until minor oozing is stopped. To assess blood loss during liver transection the suction device will be connected to a new suction container for the period of actual hepatic transection.
Blood transfusion:	Administration of blood transfusions is documented for the intraoperative and postoperative period until 48 hours postoperatively. Documentation includes number of patients who received blood transfusions as well as amount of transfused packed red blood cells (PRBC) [units].
Operation time [min]:	Time from skin incision to placement of last skin staple/suture.
Liver transection time [min]:	Time from beginning to end of liver transection.
Duration of postoperative hospital stay [days]:	Time from day of operation to day of discharge.
Duration of ICU stay [days]:	Time on the Intensive Care Unit (ICU). Patients' stay in the recovery room and Intermediate Care (IMC) unit exceeding 24 hours is considered as ICU stay.

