### Methods against Bias

#### Randomization

Patients are screened consecutively and all eligible patients are included into the trial. In order to achieve comparable groups and ensure allocation concealment patients are randomly allocated to the study groups. A block randomisation list is generated by the Institute for Medical Biometrics and Informatics (IMBI) applying SAS (SAS™ Version 9.1., SAS Institute Inc., Cary, USA). Randomization is carried out intraoperatively in case resectability is given. Randomization is carried out using opaque and sealed envelopes that are consecutively numbered. Block randomization will be performed for each center to achieve equal group sizes per center. The details of randomization will be kept in safe and confidential. Subjects withdrawn from the trial retain their identification codes (e.g. randomization number). New subjects receive a new identification code.

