### Sample size

The sample size is based on the primary outcome parameter and the primary analysis. Internal observations (Department of Surgery, University of Heidelberg) showed a mean intraoperative blood loss of 700 ml for patients undergoing stapler hepatectomy with a sample standard deviation of about 550 ml [19]. To detect a clinically relevant absolute difference reduction in intraabdominal blood loss of 280 ml with significance α = 5% and a power of (1-β) = 80% n = 122 patients have to be randomized in the study (n = 61 patients per group) using two-sided t-test. Considering an estimated intraoperative drop-out rate of about 10% (e.g. unexpected death prior to beginning of transection, protocol violations) eight additional patients will be randomized and the total sample size accounts for n = 130 patients (n = 65 patients per group).

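### The confirmatory ANCOVA adjusts for CVP during transection, a post-randomisation value that technique or bleeding can change, so it need not estimate the ITT effect and its claimed power is not assured

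*Protocol article*

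**What the plan says.** **Timing.** Under Randomization: "Randomization is carried out intraoperatively in case resectability is given". Allocation therefore precedes transection.

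**Outcome.** Study objectives and endpoints defines the primary endpoint as "total intraoperative blood loss [ml], which is defined as blood loss from skin incision until closure of the skin". The whole transection lies inside this window.

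**Model.** Statistical analysis sets a null hypothesis of equal mean blood loss and an intention-to-treat analysis of every randomised patient. The ANCOVA has "area of resection and CVP during transection as continuous covariates and type of intervention as factor". On power it adds that "it can be assumed that evaluation with analysis of covariance has the same or even higher power".

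**CVP.** Standardisation of treatments describes lowering CVP for transection by fluid restriction and caval clamping, with further measures if these are not enough. Blinding states that the operating team cannot be blinded.

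**Area.** "The transection area will be assessed using an imprint of the resected specimen on a paper sheet", so this value is also obtained after the allocated technique has been used.

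**Patients without transection.** The drop-out allowance under Sample size gives as one example "unexpected death prior to beginning of transection".

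**The concern.** The null hypothesis concerns the total effect of technique on blood loss. A covariate-adjusted comparison targets that effect when treatment does not affect the covariates. Values fixed before randomisation meet this condition by design. CVP during transection does not. It is taken while the randomised technique is in use, and it may respond to technique, to bleeding or to how the team manages volume.

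Two routes matter, with different consequences:

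- **Bleeding changes CVP.** The covariate is then partly a consequence of the outcome, and adjusting for it removes part of a real effect.
- **Technique changes CVP by another path**, for example through transection time or fluid handling. The adjusted contrast is then displaced in either direction, and the test can reject too often when technique has no total effect.

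The power statement depends on the same condition but is made without it. No other confirmatory analysis is stated, so the trial's main conclusion rests on this model.

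**Working it through.** **1. The plan's own figure.** Inputs from Sample size: difference 280 ml, SD 550 ml, two-sided α 5%, power 80%.

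n per arm = 2 × (1.960 + 0.842)² × (550/280)² = 2 × 7.85 × 3.858 ≈ 60.6, so 61 per arm and 122 in total. This matches "n = 61 patients per group) using two-sided t-test". Exact (noncentral t) power at 61 per arm is 79.6%. The sample size is not at issue.

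**2. Covariates that treatment does not affect.** With covariates explaining a share R² of the within-arm variance, the residual SD is 550 × √(1 − R²). Power at 61 per arm:

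| R² | Power |
|---|---|
| 0 | 79.6% |
| 0.1 | 83.6% |
| 0.2 | 87.7% |
| 0.3 | 91.5% |

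Under this condition the power sentence is sound.

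**3. General formula when treatment moves a covariate.** Let r be the within-arm correlation of covariate and blood loss, and d the standardised between-arm shift in the covariate.

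Adjusted effect = total effect − r × 550 × d.

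The documents give neither r nor d. All values below are assumptions.

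**4. CVP reacts to blood loss.** The shift is then d = r × 280/550, so the adjusted effect is 280 × (1 − r²). If area, unaffected by treatment, explains 20% of the variance, the same algebra gives 280 × (1 − r²)/(1 − 0.2r²). Power is by simulation at 61 per arm.

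| r | Estimate, area explains nothing | Power | Estimate, area explains 20% | Power |
|---|---|---|---|---|
| 0.3 | 280 × 0.91 = 255 ml | about 74% | 280 × 0.91/0.982 = 259 ml | about 83% |
| 0.4 | 280 × 0.84 = 235 ml | about 71% | 280 × 0.84/0.968 = 243 ml | about 82% |
| 0.5 | 280 × 0.75 = 210 ml | about 66% | 280 × 0.75/0.95 = 221 ml | about 78% |

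With no treatment effect, rejection stays near 5% (simulated 4.3% to 5.4%). CVP is then independent of arm.

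In the right-hand columns, area alone would give 87.7%. Adding CVP therefore costs about 5 to 10 points (87.7 − 83 and 87.7 − 78), even where power stays above 80%.

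**5. Technique shifts CVP by 0.25 SD, with no true total effect.** Bias = r × 550 × 0.25.

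| r | Bias | Rejection (nominal 5%) |
|---|---|---|
| 0.3 | 41 ml | 7.1% |
| 0.4 | 55 ml | 9.1% |
| 0.5 | 69 ml | 12.3% |

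With a true effect of 280 ml and the same shift, the estimate is 239 to 211 ml (power 70% to 67%) if the shift carries part of the benefit. It is 321 to 349 ml (power 91% to 98%) if the shift runs the other way.

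**6. Patients without transection.** Blood loss counts from skin incision, so such a patient can have an outcome. There is no CVP during transection and no specimen, so neither covariate exists.

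**The case against.** **Late measurement is not itself bias.** This is correct. What matters is whether treatment affects the covariate. If it moves neither, power at 61 per arm is 81% to 90% for r from 0.2 to 0.5, and the estimate stays at 280 ml. A reader might infer that the power claim is false. The documents do not show that; they show only that its condition is not secured.

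**CVP is held to a common low target in both arms, with otherwise identical care.** This narrows its range and may make both r and d small. The article also does not say at what moment the CVP value is taken, and a reading at the very start of transection would precede most transection bleeding. That CVP responds to bleeding is an inference, not something the protocol states. These points limit the likely size. They do not turn the covariate into a baseline value, because the plan names CVP during transection.

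**A reader might infer that the adjustment generally produces false positives.** It does not if CVP only reacts to blood loss. Inflation needs technique itself to shift CVP.

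**A reader might treat specimen area as equally serious.** The protocol shows no route from technique to cut surface, both techniques must be feasible at entry, and there is a prognostic reason to adjust. Area is probably set mainly by the planned resection, so the risk is smaller.

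**Nor do the sections that mention only area contradict the analysis section.** Neither says that area is the sole covariate.

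**Missing covariates.** The text does not state a complete-case analysis, and handling may be left to the SAP. This part is secondary.

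**Conclusion.** The concern holds for CVP during transection. The confirmatory model conditions on a value that the design leaves open to influence from technique and from the outcome, so it need not estimate the total effect named in the null hypothesis. At 61 per arm, SD 550 ml and a true effect of 280 ml:

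- If CVP reacts to blood loss (r 0.3 to 0.5), the effect is understated by about 25 to 70 ml. Power depends heavily on how much area explains, and type I error is preserved.
- If technique shifts CVP by 0.25 SD, type I error can rise to between 7% and 12%.

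The values of r, d and the variance explained by area are all assumed, so neither the direction nor the size of any bias can be known in advance. The power sentence is not assured, which is weaker than saying that it is wrong. Specimen area shares the timing problem at lower risk. A patient who dies before transection has neither covariate, which sits badly with analysing everyone randomised, but this adds to the main point rather than carrying it.

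**What to change.** 1. Remove CVP during transection from the confirmatory ANCOVA.
2. Adjust only for values fixed before the envelope is opened: planned resection extent from preoperative imaging and intraoperative ultrasound and, if wanted, CVP recorded at randomisation. If these are recorded for everyone at that point, each randomised patient has complete covariates, including one who never reaches transection.
3. Keep the model with specimen area and CVP during transection as a pre-specified sensitivity analysis.
4. Restrict the power sentence to pre-randomisation covariates.

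**Cost.** Revised analysis wording and one or two extra entries at randomisation. Neither the sample size nor the conduct of the operation changes. The drawback is precision: planned extent may explain less variance than the measured area, and CVP at randomisation may precede its lowering and so be less prognostic than the value during transection.

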### Data management and quality assurance

The investigator or a designated representative enters all protocol-required information in the case report form (CRF). The CRF should be completed as soon as possible after the information is collected, preferably on the same day when a trial subject is seen for an examination, treatment, or any other trial procedure. The reason for missing data should be provided. The investigator is responsible for ensuring that all sections of the CRF are completed correctly and that entries can be verified in accordance with the source data.

The completed CRF must be reviewed and signed by the investigator named in the trial protocol or by a designated sub-investigator. The principle investigator will retain originals of all CRF at the end of the trial

Monitoring within the CRUNSH Trial is carried out by an independent investigator at the Department of Surgery, University of Heidelberg, who is not involved in the trial and in completing the CRFs. The basic data of all participating patients are completely checked, i.e. existing patient, patient number, initials, the availability of signed informed consent. For a proportion of 10% of the study participants (randomly selected) a complete check of all data in the CRF (i.e. a 100% clinical source data verification; SDV) is carried out. The extent of further SDV is dependent on the quality of the data and occurrence of protocol violations.

### Ethical and legal considerations

The study is conducted in agreement with either the Declaration of Helsinki (Tokyo, Venice, Hong Kong, Somerset West and Edinburgh amendments) or the laws and regulations of the country, whichever provides the greatest protection of the patient. The protocol has been written, and the study will be conducted according to the ICH Harmonized Tripartite Guideline for Good Clinical Practice (ref: http://www.ich.org/fileadmin/Public_Web_Site/ICH_Products/Guidelines/Efficacy/E6_R1/Step4/E6_R1__Guideline.pdf).

The trial protocol is approved by the local independent ethics committee of the University of Heidelberg approved the trial protocol, the patient information and informed consent sheet.

The CRUNSH Trial is registered at the ClinicalTrials.gov protocol registration system (NCT01049607).

All patients will be informed of the aims of the study, the possible adverse events, the procedures and possible hazards to which he/she will be exposed to, and the mechanism of treatment allocation. They will be informed as to the strict confidentiality of their patient data, but that their medical records may be reviewed for trial purposes by authorized individuals other than their treating physician. The signed consent document is kept by the investigator. A copy of the signed consent document is handed out to the subject or the subject's legally authorized representative.

It will be emphasized that the participation is voluntary and that the patient is allowed to refuse further participation in the study whenever he/she wants. This will not influence the patient's subsequent care. Documented informed consent must be obtained for all patients included in the study before they are registered or randomized in the study. This must be done in accordance with the national and local regulatory requirements.

It is the responsibility of the investigator to maintain patient's confidentiality. During the trial, patients will be identified solely by means of their initials, age and individual identification code (screening number, randomization number). Trial findings will be stored in accordance with local data protection law/ICH GCP Guidelines and will be handled in strictest confidence. For protection of these data, organizational procedures are implemented to prevent distribution of data to unauthorized people.

The investigator will maintain a personal subject identification list (screening numbers with the corresponding subject names) to enable records to be identified.

## Abbreviations

**ALT**: Alanine aminotransferase; **AST**: Aspartate aminotransferase; **ANCOVA**: Analysis of covariance; **CRF**: Case Report Form; **CV**: Curriculum vitae; **CVP**: Central venous pressure; **GCP**: Good Clinical Practice; **GGT**: Gamma glutamyl transpeptidase; **ICH**: International Conference on Harmonization of Technical Requirements for Registration of Pharmaceuticals for Human Use; **INR**: International normalized ratio; **IVC**: Inferior vena cava; **POD**: Postoperative day; **PRBC**: Packed red blood cells; **RCT**: Randomized controlled trial; **SDV**: Source Data Verification
